#### Implementation outcomes

Penetration is the primary implementation outcome and is defined as the proportion of SLNB procedures performed using ICG as a single tracer during Phase III, relative to the total number of SLNB procedures performed on the target population in that phase. The numerator consists of all Phase III SLNB procedures performed with ICG only, and the denominator is derived from aggregated sources such as procedural codes.

Adoption is assessed at both hospital and provider levels. Hospital-level adoption is defined as the proportion of participating hospitals performing SLNB with ICG as a single tracer in Phase III. Provider-level adoption is the proportion of surgeons performing SLNB with ICG as a single tracer in Phase III relative to all surgeons performing SLNB. Entry into Phase II (dual-tracer use) reflects initial adoption, and exclusive ICG use in Phase III indicates full adoption. Continued dual-tracer use beyond Phase II is considered delayed adoption, and reversion to ^99m^Tc-nanocolloid is classified as relapse.

Fidelity is measured intraoperatively through surgeon self-reporting of deviations from the ICG-guided SLNB protocol and their rationale for these deviations.

Appropriateness, feasibility and acceptability are assessed using a structured healthcare-provider questionnaire administered 3 months into Phase III. Although generic instruments for implementation outcomes are available, these are not tailored to the clinical and organisational context for ICG-guided SLNB and may not adequately capture procedure-specific, workflow-related and organisational determinants relevant to this setting.^56 57^ Therefore, a context-specific questionnaire was developed using a CFIR-informed approach, supplemented by determinants derived from the Measurement Instrument for Determinants of Innovations framework and factors identified in the SLNB and ICG-fluorescence literature.^19 49 58^ Questionnaire items were designed to operationalise Proctor’s implementation outcomes in a manner relevant to the current clinical context. The instrument was co-developed by researchers and oncological surgeons with expertise in ICG fluorescence and iteratively refined based on feedback from implementation scientists and value-based healthcare experts. Pilot testing with end-users ensured clarity and validity. The final questionnaire comprises Likert-scale items, multiple-choice questions and open-ended questions, enabling concurrent collection of quantitative data with complementary qualitative insights.

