### Study population

Patients aged ≥18 years with ductal carcinoma in situ (DCIS) or biopsy-confirmed invasive T1–T3 breast cancer are eligible if clinically node-negative as confirmed by preoperative axillary ultrasound and if there is an indication for breast surgery with SLNB via axillary incision. Exclusion criteria include combined marking of the axillary node with a radioactive iodine seed procedure, known allergy to ICG, iodine or intravenous contrast agents, prior axillary lymph node dissection (ALND), hyperthyroidism or thyroid cancer, pregnancy or breast-feeding and absence of informed consent.

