### Outcomes and outcome measures

Following the framework of Proctor *et al,*^50^ outcomes are categorised into three domains: implementation outcomes (penetration, adoption, fidelity, appropriateness, feasibility and acceptability), intervention outcomes (effectiveness, safety and costs) and patient-reported experience (patient satisfaction). Table 1 provides an overview of all outcomes, definitions, outcome measures and data sources or instruments.

**Table 1 T1:** Overview of implementation, intervention and patient-reported experience outcomes with corresponding definitions, outcome measures and data sources

Implementation outcomes	Definition	Outcome measure	Data source/instrument
Adoption	Intention, initial decision or action to try or employ ICG fluorescence	Proportion of hospitals performing SLNB with ICG only (Phase III) Proportion of surgeons performing SLNB with ICG only (Phase III)	Quantitative: hospital administrative data
Penetration	Integration of a practice within a service setting and its subsystems	Proportion of SLNB procedures performed with ICG only relative to all SLNBs in the target population (Phase III)	Quantitative: hospital administrative data
Fidelity	Degree to which ICG fluorescence is implemented as intended	Proportion of SLNB procedures conducted according to protocol (Phase III) Number, type and reasons for protocol deviations related to ICG preparation, storage and administration (Phase III)	Intraoperative healthcare provider questionnaire with embedded open-text fields (Phase III)
Appropriateness	Healthcare providers perceived fit, usefulness and relevance of ICG fluorescence for identifying the SLN	Perceived relevance Perceived strength of evidence Reliability of ICG fluorescence Patient-specific suitability Overall level of appropriateness	Healthcare provider questionnaire (REDCap) with embedded open-text fields (Phase III)
Feasibility	Extent to which ICG fluorescence can be successfully used within a given setting	Site readiness (availability of fluorescence imaging equipment) Ease of learning Experience with dual-tracer SLNB prior to transitioning to ICG only Confidence in transitioning to ICG only Suitability for routine clinical practice Team attitude and motivation Collaboration with nuclear medicine Overall level of feasibility	Healthcare provider questionnaire (REDCap) with embedded open-text fields (Phase III)

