### Sample size

A formal sample size calculation was not performed, as the INFINITE trial primarily aims to implement ICG-guided SLNB in routine clinical practice, while concurrently collecting real-world data on effectiveness. Moreover, sample size estimation for stepped-wedge cluster designs is inherently challenging due to the sequential rollout across clusters.^41^ Instead, the study uses a convenience sample of real-world data from seven purposefully selected hospitals.

The seven participating hospitals collectively perform approximately 1500 SLNBs via axillary incision annually. Over the planned study period, this corresponds to approximately 2250 SLNB procedures. Given the limited exclusion criteria and an anticipated exclusion rate of ≤10%, approximately 2025 patients are expected to be eligible. Based on practical feasibility and consent rates observed during the early study phase, approximately 850 patients are expected to be included. The estimate is informed by initial inclusion patterns and may vary modestly over time as site-specific workflow stabilises.

The anticipated sample size is considered sufficient to estimate key quantitative outcomes with acceptable precision. For the primary implementation outcome, penetration, an expected Phase III sample of approximately 280 SLNB procedures yields a 95% CI of roughly ±6 percentage points when the proportion is near 50%, with narrower intervals for lower or higher values, based on binomial approximation. For effectiveness outcomes, assuming a per-case SLN detection rate of approximately 95% in Phase III, the corresponding 95% CI would be approximately ±2–3 percentage points. This level of precision is appropriate for pragmatic hybrid effectiveness-implementation research, in which the aim is to describe real-world uptake and contextual variation rather than to formally test hypotheses.

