### Ethics and dissemination

This study is subject to the Dutch Medical Research Involving Human Subjects Act (Wet medisch-wetenschappelijk onderzoek met mensen, WMO). Ethical review and approval were obtained from the Medical research Ethics Committees United (MEC-U; Central Committee on Research Involving Human Subjects dossier number NL87551.100.24; approval date 6 November 2024). The study was prospectively registered at ClinicalTrials.gov (NCT07146295) and in the Dutch Trial Register (Landelijk Trial Register; LTR; NL-005321). The boards of directors of all participating hospitals approved local participation in the study.

Written informed consent will be obtained from all participating patients. Consent is required because the study involves prospective data collection for research purposes and because the tracer used for SLNB may differ from standard practice during the phased implementation. Patients will be informed about the study objectives, procedures, potential risks and benefits, data handling and their right to withdraw without consequences for their care.

The study is considered low risk. ICG has an established safety profile, is non-ionising and is widely used in clinical practice for other indications.^63^ Adverse events potentially related to ICG use will be monitored and recorded throughout the study. The trial will be conducted in accordance with the principles of the Declaration of Helsinki and Good Clinical Practice guidelines.

Study results will be disseminated through publication in open-access, peer-reviewed scientific journals and presentation at national and international conferences focusing on oncological surgery, breast cancer care and/or image-guided surgery. In addition, implementation products developed within the study, including a clinical protocol, implementation guide, educational materials and patient information resources, will be made publicly available to support national scale-up.

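### Penetration is defined over all Phase III SLNBs in the target population, but its stated precision uses the included-patient count of about 280, and the place of non-consenters in that population is left in conflict

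*Protocol article*

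**What the plan says.** The Implementation outcomes section defines penetration as ICG-only procedures in Phase III "relative to the total number of SLNB procedures performed on the target population in that phase". It adds: "The numerator consists of all Phase III SLNB procedures performed with ICG only", and "the denominator is derived from aggregated sources such as procedural codes". Table 1 gives the same ratio and names hospital administrative data as its source. Step 6 of the integrated implementation approach gives the purpose: to assess how far ICG replaces the radioisotope in the participating sites.

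The Sample size section moves from about 1500 SLNBs a year to 2250 over the study, then to 2025 eligible after an exclusion rate of at most 10%. It continues: "Based on practical feasibility and consent rates observed during the early study phase, approximately 850 patients are expected to be included". For penetration it states that "an expected Phase III sample of approximately 280 SLNB procedures yields a 95% CI of roughly" ±6 percentage points when the proportion is near 50%.

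The Study population section ends its exclusion list with "pregnancy or breast-feeding and absence of informed consent". The Ethics and dissemination section says consent is required partly "because the tracer used for SLNB may differ from standard practice during the phased implementation".

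**The concern.** The definition points to every SLNB in the target population, whether or not the patient joined the study. The precision statement for the same outcome appears to rest on study participants only. The eligibility text does not settle which is meant. If absence of consent is an exclusion, non-consenters fall outside the study population. Yet the Sample size section removes at most 10% for exclusions, calls the rest eligible, and only then brings in consent.

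This is the trial's single primary outcome, and it is reported as one proportion with a CI and no comparison. Nothing else in the analysis would show a reader which population the figure describes. A proportion among participants and a proportion among all SLNBs at the sites answer different questions, and only the second matches the purpose given in Step 6.

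**Working it through.** **Inputs.** From the Sample size section: 1500 SLNBs a year, 2250 in total, 2025 eligible, 850 included, 280 in Phase III. From the design, timeline and Figure 1 caption: 18 months, clusters of 2, 3 and 2 hospitals, 3-month steps, a fixed 6-month Phase II. Two assumptions are added: equal volume per hospital, and the first cluster entering Phase II at month 3.

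**1. Funnel.** 1500 × 1.5 = 2250, and 2250 × 0.9 = 2025, both as stated. Included share: 850/2025 = 42% of eligible, or 850/2250 = 38% of all procedures. If non-consent counted fully as an exclusion, the excluded share would be far above the stated 10%.

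**2. Phase III share.** The clusters spend 9, 6 and 3 months in Phase III. In hospital-months: (2×9 + 3×6 + 2×3)/(7×18) = 42/126 = 1/3.

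**3. Which population gives 280?**
- Included: 850/3 = 283
- Eligible: 2025/3 = 675
- All procedures: 2250/3 = 750

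Only the included count matches. If the first transition were at month 6, the share would be 1/6 and the included count 850/6 = 142, which does not fit 280. This supports the month-3 assumption.

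**4. The article's own precision.** Half-width = 1.96 × √(p(1−p)/n).
- n = 280, p = 0.50: 5.9 points, reproducing ±6.
- n = 280, p = 0.95: 2.6 points, reproducing the ±2–3 stated for SLN detection.

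**5. Precision under the written definition, p = 0.50.**
- n = 675: 3.8 points.
- n = 750: 3.6 points.

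Because the exclusion rate is given as at most 10%, the eligible count lies between these two. These are the article's own simple binomial half-widths, with no allowance for clustering by hospital.

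**6. What would follow if the populations were mixed (conditional, not the stated plan).** With a numerator from included patients only and a denominator from codes, the ceiling is 280/675 = 41% on eligible procedures, or 280/750 = 37% on all procedures, even if every included patient had ICG alone. With both terms from included patients only, the ratio could take any value up to 100%, but it would describe participants rather than sites.

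**The case against.** The written definition is better than the concern might suggest. The numerator is all Phase III ICG-only procedures, with no consent limit. The denominator comes from aggregated sources, and Table 1 gives administrative data as the only source for penetration. The Data collection section mentions intraoperative case report forms for implementation outcomes, but it refers to Table 1, which ties the intraoperative form to fidelity. On this reading numerator and denominator already match, and if non-consenters are treated like participants every base gives the same percentage. The ±6 points are also wider than needed, no hypothesis is tested, and no decision depends on 280. Extraction rules can be left to a fuller document.

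Most of this stands. A reader might infer that the same practice could be reported as about 34% or about 90%, so that the primary outcome would really measure consent. The documents do not support that. The contrast needs an assumed 90% ICG-only rate among included patients (252 of 280, against 252/750 = 34%), and the article gives no expected penetration. It also needs a study-form numerator for the low figure and a participants-only denominator for the high one, and neither is stated. If non-consenters keep the radioisotope, a low figure over all SLNBs would be the true share, not an artefact. Nor is the shortfall from 2025 to 850 all refusal, since the article also cites practical feasibility.

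The objection does not remove the mismatch itself. The n and CI given for penetration belong to a population other than the defined one, and the exclusion list conflicts with the eligible count on where non-consenters stand.

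**Conclusion.** The point holds as an inconsistency in the population of the primary outcome. The stated n of about 280 is the expected number of included Phase III patients. The definition implies about 675 to 750, larger by a factor of 2.4 to 2.7. The matching half-width at 50% is about ±3.8 to ±3.6 points instead of ±6. The error is conservative: the sample is not too small, it is the wrong population for this outcome.

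The counts rest on equal hospital volumes and a first transition at month 3. The ceilings of 37% to 41%, and the loss of meaning if only participants are counted, are risks under readings that the text leaves open. They are not what it plans.

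**What to change.** 1. In the penetration definition, state that the target population is all clinically eligible Phase III SLNBs via axillary incision, regardless of study consent. Make clear that absence of consent excludes a patient from individual data collection but not from this count.
2. Take numerator and denominator from the same hospital administrative source, as aggregate Phase III counts by tracer used. If a source cannot remove clinical exclusions, say so and name the base actually used.
3. Report penetration among included patients separately and label it as such.
4. In the Sample size section, restate n and CI for penetration only: about 675 to 750 procedures, ±3.8 to ±3.6 points at 50% by the same binomial approximation. Keep 280 for the SLN detection rate, whose data come from included patients and whose ±2–3 points is correct.

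The cost is a few sentences and a small extra data extraction per hospital, from a source that Table 1 already names.

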#### Phase II (transition period)

During the transition period, both ICG and ^99m^Tc-nanocolloid are administered. Preoperative preparation at the Nuclear Medicine Department mirrors Phase I, with the exception that skin markings are omitted and surgeons are blinded to lymphoscintigraphy results. Intraoperatively, the SLNB is guided primarily by ICG, with ^99m^Tc-nanocolloid serving as a within-patient control.

ICG is administered as described in the ICG administration section. A caudal axillary incision is made 5–30 min after injection, and SLNB is performed before breast tumour resection. Lymphatic channels may be clipped to prevent ICG leakage. The SLN is defined as the LN with the highest fluorescent signal and is excised first. The axilla is subsequently inspected for residual fluorescent LNs; if present, up to two additional LNs may be excised. All excised LNs are assessed ex vivo for ^99m^Tc uptake. The axilla is then explored for residual ^99m^Tc activity using the gamma probe, supplemented by inspection and palpation. Additional LNs are excised in accordance with the predefined limit of two.

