#### Phase III (post-implementation period)

SLNB is performed using ICG as a single tracer, following the same technique as described for Phase II but without concurrent use of ^99m^Tc-nanocolloid as a within-patient control. This approach eliminates the need for a preoperative visit to the Nuclear Medicine Department.

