Several limitations should be acknowledged. Cluster transitions are based on site readiness rather than random allocation. Although reflecting real-world implementation, a non-randomised comparison between pre- and post-implementation phases may be influenced by temporal trends or learning effects within the study period. Yet, the relatively short trial duration and stable clinical context limit the likelihood that such trends materially affect this comparison. The questionnaire-based implementation outcomes (appropriateness, feasibility and acceptability) are formally assessed at a single time point in Phase III. This timing was chosen so that providers can accumulate sufficient experience to give an informed appraisal, but it may limit characterisation of how these outcomes evolve during implementation. Some implementation outcomes, such as fidelity, rely on surgeon self-reporting and may be subject to reporting bias. The sample size is determined by feasibility rather than formal power calculations, which may limit precision for selected secondary outcomes. Although the study includes in-hospital data and collects patient-incurred costs, it is not designed to provide a full societal cost-effectiveness analysis.

Finally, the trial is also conducted in an evolving axillary management landscape, in which recent and ongoing trials suggest that axillary de-escalation, including omission of SLNB, may be safe in selected patients.^64^,^67^ However, this evidence base remains limited, and uptake in routine practice is cautious. SLNB remains indicated for many patients, underscoring the continued need for safe, efficient and consistently implemented techniques.

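### Fidelity depends on surgeons declaring deviations, its scope differs between the text and Table 1, and no recorded value (such as node count) is used to check it

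*Protocol article*

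**What the plan says.** Under Implementation outcomes, the protocol article defines the outcome thus: "Fidelity is measured intraoperatively through surgeon self-reporting of deviations from the ICG-guided SLNB protocol", together with the surgeon's reasons for them. The definition sets no limit on the kind of deviation.

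Table 1 (Outcomes and outcome measures) gives two fidelity measures:

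- "Proportion of SLNB procedures conducted according to protocol (Phase III"), with no restriction on scope.
- "Number, type and reasons for protocol deviations related to ICG preparation, storage and administration (Phase III"), restricted to the handling of ICG.

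The source named for both is "Intraoperative healthcare provider questionnaire with embedded open-text fields (Phase III").

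The surgical technique is set out under Phase II (transition period). For timing and sequence it says: "A caudal axillary incision is made 5–30 min after injection, and SLNB is performed before breast tumour resection". It also has the node with the strongest signal excised first and allows up to two further nodes. Phase III is performed "following the same technique as described for Phase II", without the radioactive tracer.

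The effectiveness rows of Table 1 list total node yield per procedure in all phases. Providers collect these data during surgery, with additions from the patient file. Quantitative analysis plans fidelity as descriptive proportions with counts. Strengths and limitations concedes: "Some implementation outcomes, such as fidelity, rely on surgeon self-reporting and may be subject to reporting bias".

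**The concern.** There are two linked problems.

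The first is scope. A technique deviation counts against the first Table 1 measure, but the second measure, which should say what kind of deviation it was and why, covers only ICG handling. The proportion and its explanation therefore describe different sets of events.

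The second is that a procedure is classed as faithful unless the surgeon says otherwise. Failure to declare moves the estimate in one direction only, upward. For at least one technique element, the node limit, the information needed to detect an undeclared departure is already collected, but the article does not use it for fidelity.

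Clinical impact gives fidelity, together with appropriateness, feasibility and acceptability, the task of explaining why uptake goes well or badly at different sites. The trial's implementation guide and clinical protocol are meant to support national scale-up. A fidelity figure that is too high, with no breakdown of technique deviations, would inform those products less well than the data allow.

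**Working it through.** **Plan's own figures.** The article gives no expected rate, target or precision for fidelity, so there is nothing to reproduce for that outcome. The only precision figures for Phase III are in Sample size, for about 280 procedures. With half-width = 1.96 × √(p(1 − p)/n):

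- p = 0.50, n = 280: 1.96 × √(0.25/280) = 5.9 points (article: roughly ±6).
- p = 0.95, n = 280: 1.96 × √(0.0475/280) = 2.6 points (article: ±2–3).

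Both reproduce. They serve below only as a yardstick for sampling error.

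**Scope, side by side.**

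| Place | Scope |
|---|---|
| Implementation outcomes, definition of fidelity | whole ICG-guided procedure |
| Table 1, first measure (proportion) | whole procedure |
| Table 1, second measure (number, type, reasons) | ICG preparation, storage, administration only |

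The third row does not match the other two.

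**Which technique elements could be checked from the items the article lists?**

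| Element | Listed recorded item that tests it |
|---|---|
| Limit on additional nodes | total nodes excised, all phases |
| Injection-to-incision interval | none; detection time and SLNB duration both start at incision |
| SLNB before tumour resection | none |
| Strongest-signal node first | none |
| Caudal incision | none |

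Only the node limit can be tested. Reading the limit as one sentinel node plus two, a Phase III procedure with five nodes exceeds it. It would still count as according to protocol if no deviation were declared.

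**Size.** Let d be the true share of procedures with a deviation and s the share of those that surgeons declare. Assume that no surgeon declares a deviation that did not occur. Then

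reported fidelity = 1 − d × s, true fidelity = 1 − d, overstatement = d × (1 − s).

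The article gives neither d nor s, so both are assumed:

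| d | s | True | Reported | Overstatement (points) |
|---|---|---|---|---|
| 5% | 0.5 | 95% | 97.5% | 2.5 |
| 10% | 1 | 90% | 90% | 0 |
| 10% | 0.8 | 90% | 92% | 2 |
| 10% | 0.5 | 90% | 95% | 5 |
| 10% | 0 | 90% | 100% | 10 |
| 20% | 0.5 | 80% | 90% | 10 |
| 20% | 0 | 80% | 100% | 20 |

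For d = 10% the overstatement runs from 0 to 10 points; across d = 5% to 20% it runs from 0 to 20. At d = 10% and s = 0.5 it is 5 points, against a sampling half-width of 2.6 points at the reported 95%. At d = 10% and s = 0.8 it is 2 points, below the half-width of 3.2 at the reported 92%. Whether the bias exceeds sampling error therefore depends on values that the article does not supply.

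**The case against.** The case on the other side is substantial.

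- **Technique is not shut out of fidelity.** A reader might infer from the second Table 1 measure that technique departures cannot count. The documents do not support this: the definition and the proportion are unrestricted, and the questionnaire has open-text fields. A surgeon can declare such a departure. What stands is the mismatch in scope.
- **The listed data would not expose most technique departures.** A reader might suppose that a late incision would show up in the recorded times. It would not, because those times start at incision. What stands is node count.
- **The second source is not fully independent.** Providers also enter the perioperative data, and Data collection already names intraoperative case report forms among the sources for implementation outcomes. This is fair, but comparing a recorded count with a fixed limit does not require the surgeon to label the case a deviation. No section says that such a comparison is made.
- **The weakness is disclosed.** Strengths and limitations names reporting bias in fidelity. The disclosure neither reduces the bias nor mentions the difference in scope.
- **Details may sit elsewhere.** The questionnaire and the scoring rule may be in the full protocol, and an itemised checklist may exist. That is a reason not to call the rule missing. It does not remove the difference in scope, which is in the article's own text.
- **Drift has other routes to detection.** Excess node removal would appear in the Phase III node yield results, and three-monthly evaluations look for sites that need support. It would therefore be wrong to say that drift goes unseen. It could, however, go unseen in the fidelity figure.

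**Conclusion.** The point holds in a limited form. The scope of fidelity is inconsistent between the Implementation outcomes text and the first Table 1 measure on one side and the second Table 1 measure on the other. The article also describes no check of the self-report against recorded data, although one relevant item, nodes excised, is collected in every phase. Provided surgeons do not declare deviations that did not occur, any error from under-declaration is upward.

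Its size cannot be established. The illustration of 0 to 10 points rests on an assumed 10% deviation rate and the full range of declaration shares. A reader might take a particular error, such as 10 points or more, as the expected one; nothing in the article supports a specific value, and with full declaration the error is zero.

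Fidelity is secondary and descriptive, penetration is untouched, and the reporting bias is acknowledged. This is an inexpensive improvement to one outcome and does not threaten the trial's main result.

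**What to change.** 1. **Align the scope.** Give the definition under Implementation outcomes and both Table 1 measures the same whole-procedure scope, so that the number, type and reasons of deviations include technique as well as ICG handling.
2. **Add a derived flag.** Count a deviation whenever an item already recorded departs from the protocol's own stated limit, declared or not. Start with node count, and state how total nodes excised map onto the limit on additional nodes.
3. **Keep self-report** for the reasons, and for elements that the article does not list as recorded, such as the injection-to-incision interval and the order relative to tumour resection.
4. **Report both sources.** Give the proportion faithful by self-report alone and by self-report plus recorded flags, with a cross-tabulation of declared against flagged cases. For the node limit this also estimates the share of departures that surgeons declare, which is unknown at present.

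The node-count flag needs no new field. A checklist covering every technique element would need several items that the article does not list (injection time, order of resection, dose, injection sites). The trial has been running at all sites since 18 April 2025, so that is not asked for here. The cost is slightly more derivation work and probably a lower reported fidelity.
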